**Results::**

After obtaining a written informed consent, 200 adult patients undergoing coronary artery bypass grafting will be enrolled and randomised to receive either restrictive or liberal oxygenation perioperatively. The liberal oxygenation group will receive 1.0 fraction of inspired oxygen throughout the intraoperative period, including during cardiopulmonary bypass. The restrictive oxygenation group will receive the lowest fraction of inspired oxygen required to maintain arterial partial pressure of oxygen between 100 and 150 mmHg during cardiopulmonary bypass and a pulse oximetry reading of 95% or greater intraoperatively, but no less than 0.3 and not higher than 0.80 (other than induction and when the oxygenation goals cannot be reached). When patients are transferred to the intensive care unit, all patients will receive an initial fraction of inspired oxygen of 0.5, and then fraction of inspired oxygen will be titrated to maintain a pulse oximetry reading of 95% or greater until extubation. The lowest postoperative arterial partial pressure of oxygen/fraction of inspired oxygen within 48 hours of intensive care unit admission will be the primary outcome. Postoperative pulmonary complications, length of mechanical ventilation, intensive care unit stay, hospital stay, and 7-day mortality after cardiac surgery will be analysed as secondary outcomes.

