## Methods

### Study Design and Setting

This study is a prospective, observer-blinded, web-based centrally randomised, controlled, multicentre, international clinical trial to assess the relationship between intraoperative FiO_2_ and PPCs. Surgical technique will be restricted to CABG with CPB through median sternotomy to minimise variation. Arterial partial pressure of oxygen/FiO_2_ will be assessed at baseline (preoperative values), time of postoperative ICU admission as well as 4 hours, 8 hours, 12 hours, 18 hours, 24 hours, 36 hours, and 48 hours after postoperative ICU admission (Figure 1). The study will be conducted at University of Louisville Health, Louisville, KY, USA, and 5 teaching hospitals from China with a combined more than 8000 open-heart surgeries and over 1000 CABG with CPB cases per year. We have been assured fair access to research subjects to enable completion of this study within a 1-year period. Written informed consent will be obtained from each participant preoperatively.

This study is designed not to interfere with routine clinical workflow, and patients will be centrally randomised to either restrictive or liberal oxygenation groups in a 1 : 1 ratio, and the randomisation will be stratified for each centre. For blinding, the research fellows and ICU physicians who record and assess the primary and secondary outcomes as well as who manages the patients will be blinded to the randomisation group assignment. The principal investigator (PI) of each centre and the physicians who conduct the anaesthesia and monitoring intraoperatively in the operating room are unblinded due to necessary requirements for clinical care. This protocol is in accordance with the Recommendations for Interventional Trials (SPIRIT) checklist. The SPIRIT figure demonstrates the schedule of enrolment, interventions, and outcome assessment of this trial (Table 1).

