Postoperative pain management will be provided as a bolus of 25 μg fentanyl, 0.2 mg hydromorphone intravenously, a continuous opioid infusion as needed, or 5-10 mg hydrocodone or oxycodone with acetaminophen orally with the aim of a visual analogue score less than 4. The goal is to achieve adequate pain control without respiratory compromise. Only normal saline, lactated Ringer’s solution, human albumin, or cell saver blood are allowed as maintenance infusion fluids during and after surgery. Fluid infusion rate from CPB weaning until the end of surgery should be less than 10 mL kg^–1^ h^–1^ to avoid pulmonary oedema; otherwise, the patient will be withdrawn from analysis. The trigger for transfusion of allogeneic red blood cells is 7 g dL^–1^ during CPB and 8 g dL^–1^ while not on CPB. The trigger for transfusion of plasma, cryoprecipitate, and platelets is determined by the laboratory values and clinical protocols. Transfusion of more than 2 units of red blood cells (RBCs), fresh-frozen plasma, platelets, or cryoprecipitate within 48 hours of ICU admission will result in withdrawal from the study.

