After anaesthesia induction and intubation, the restrictive oxygenation group will have FiO_2_ set at a minimum of 0.3 to maintain SpO_2_ greater than or equal to 95%. If the SpO_2_ is above 95%, a 10% further reduction in FiO_2_ will be attempted to achieve the lowest possible FiO_2_ while maintaining an SpO_2_ > 95%. During CPB, a blended air/oxygen mixture will be titrated to ABG results with the goal of PaO_2_ between 100 and 150 mmHg. The liberal oxygenation group receives 1.0 FiO_2_ throughout the intraoperative period, including during CPB. After admission to ICU, all patients will receive 0.5 FiO_2_ initially and then titrated to the lowest FiO_2_ while maintaining SpO_2_ ≥ 95% until extubation. Criteria for sedation weaning include a stable heart rate and blood pressure and a chest tube output < 200 mL over the last 2 hours. Criteria for mechanical ventilation weaning trial include a rapid shallow breathing index <100, a respiratory rate < 35, an SpO_2_ > 92%, a heart rate < 140 bpm, a systolic blood pressure <180 mmHg and >90mmHg, and no anxiety or diaphoresis from increased work of breathing. Goal-directed extubation criteria will be utilised in the cardiac ICUs of study centres. These criteria include an FiO_2_ ≤ 0.40, an SpO_2_ ≥ 95%, a rapid shallow breathing index < 100, and a negative inspiratory force ≥ –20cm H_2_O. Postoperative narcotic analgesia and sedation approaches are standardised to minimise the discrepancies among the centres. After extubation, the patient may still need continuous oxygen support in the ICU or after ICU discharge, and the lowest SpO_2_/FiO_2_ ratio will be recorded daily until discharge from the hospital.

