### Statistical Analysis

#### Sample Size Calculation

A decrease of 10% in PaO_2_/FiO_2_ from the baseline is considered as clinically significant. The ARDS definition is PaO_2_/FiO_2_ less than 300 mmHg; thus, a difference of 30 mmHg of mean value of the lowest PaO_2_/FiO_2_ postoperatively between the 2 groups will be considered as clinically significant. Assuming SD of 60 mmHg, *α* = 0.05, and 80% power with 2-sided *t*-test, at least 160 subjects will be needed in total to detect a difference (80 patients in each group). Considering potential withdrawal, protocol violation, and failure to follow-up, we will aim to recruit 200 patients (100 patients in each group) for this study.

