## Discussion

There are 500 000 cardiac surgeries a year in the USA alone. Almost every patient has lung injury, and up to 25% of them develop PPCs after cardiac surgery.^13^ Most of prior studies focus on postoperative mechanical ventilation strategies and incidence of PPCs and mortality in the ICU.^14,15^ Postoperative pulmonary complications are mainly attributed to ventilation-induced lung injury (VILI) and ventilator-associated pneumonia (VAP). Both VILI and VAP are highly time dependent and are most common in patients who are ventilated for longer than 48 hours postoperatively. A protective mechanical ventilation strategy or an adaptive support ventilation triggered by spontaneous breathing is wildly accepted and applied to wean patients in the ICU.^15, 16^ Nowadays, patients are usually extubated within 6 hours postoperatively after an uneventful CABG. Therefore, the intraoperative mechanical ventilation has become an important proportion of overall mechanical ventilation.^17,18^ Therefore, the intraoperative ventilatory management might have significant impacts on outcomes after CABG even more than the ICU management.

Several studies suggest that a protective ventilation strategy is beneficial and can reduce PPCs, but some studies found no improvement or even increased mortality in cardiac patients with the protective ventilation strategies.^5,19^ The most significant ventilation parameter change between intra- and postoperative period is FiO_2_, and scarce data currently exist to evaluate the relationship between intraoperative FiO_2_ and PPCs in cardiac surgery.

Previous studies on FiO_2_ have diverse definitions of hyperoxia. Some studies’ criteria for hyperoxia are in the normoxia range for other studies.^20^ There are no well-established PaO_2_ targets on CPB, and clinical practice is highly variable. Based on the oxygen haemoglobin dissociation curve of normal subjects, SpO_2_ decrease from 100% to 90% will decrease PaO_2_ by 40 mmHg. We choose a minimum SpO_2_ of 95% as our safe threshold because it is close to PaO_2_ 80mmHg. The PaO_2_ from ABG is more accurate and reliable but cannot be monitored continuously; thus SpO_2_ is a more feasible and appropriate index for FiO_2_ adjustments.

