The major limitation of this study lies in the difficulty of balancing many confounding factors during CABG with CPB that are harmful to the lungs, including the surgical procedure, CPB, hypothermia, blood contact with artificial surfaces, ischaemia–reperfusion injury, administration of blood products, and lung collapse.^21^ In our protocol, if the patient develops haemodynamic instability which requires a return to CPB or suffers circulatory arrest, they will be withdrawn from the study. We will also withdraw patients who require mechanical circulatory support systems like extracorporeal membrane oxygenation, ventricular assist device, or an Impella device for similar reasons. Transfusion is common in cardiac surgery, but CABG has a relatively low transfusion rate compared to other open-heart surgeries.^22^ Transfusion-associated lung injury (TRALI) has been well defined, and it is a prominent factor for increased morbidity and mortality.^23,24^ The reported incidence of TRALI varies widely, ranging from 0.0008% to 1.2% per unit of blood product administered and from 0.08% to 8% per transfused patient.^25^ Since transfusion of blood products, in particular blood plasma, may cause lung injury, these patients will also be withdrawn from our analysis. We predict a high rate of withdrawal, not only for safety reasons but also for bias control and balancing of confounding factors. Another study limitation is our inability to blind the anaesthesiologist. Only ICU physicians and research fellows/study coordinators who assess the outcomes will be blinded.

There exists increasing evidence that a restrictive oxygenation strategy may be beneficial in various groups of patients.^26^ It is important to understand the relationship between FiO_2_ and lung injury after cardiac surgery. This is one of the first randomised controlled trials to prospectively evaluate the influence of high inspired oxygen concentrations on pulmonary outcomes and oxygenation after cardiac surgery.

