## Figures and Tables

**Figure 1. f1-tjar-51-2-112:**
[figure not shown]
Algorithm and timetable for enrolment, allocation to restrictive or liberal oxygenation groups, intraoperative management, and postoperative data collection.

**Table 1. t1-tjar-51-2-112:** The Schedule of Enrolment, Interventions, and Outcome Assessment in Different Periods of This Trial

	Enrolment	Allocation	Post-allocation			Close-out
Timepoint	Preoperative 1 Day Before Surgery	Before Oxygenation	Intraoperative	Postoperative 0 hours, 4 hours, 8 hours,12 hours, 24 hours, 48 hours	Discharge	Postoperative 7 Days
Enrolment						
Eligibility screen	**X**					
Informed consent	**X**					
Allocation		**X**				
Interventions						
Restrictive oxygenation group			**X**			
Liberal oxygenation group			**X**			
Assessments						
PaO_2_/FiO_2_ (ABG)		**X**	**X**	**X**		
Postoperative pulmonary complications				**X**	**X**	
Length of mechanical ventilation					**X**	
ICU stay					**X**	
Hospital stay					**X**	
Mortality						**X**

ABG, arterial blood gas; ICU, intensive care unit.

**Table 2. t2-tjar-51-2-112:** Inclusion, Exclusion, and Withdrawal Criteria

Inclusion and Exclusion Criteria	Withdrawal Criteria
Inclusion criteria	Preoperative
Age from 18 to 80 BMI from 20 to 39.9 Isolated CABG CPB planned Median sternotomy approach Subsequent admission to ICU	Onset of heart failure Onset of acute decompensated arrhythmia Onset of low oxygen saturation (SpO_2_ < 90%) on supplemental oxygen
Exclusion criteria Severe COPD (PaCO_2_ > 60 mmHg) Recent acute coronary syndrome (<1 week) Acute onset of heart failure Severe anaemia (haemoglobin < 8 g dL^–1^) Preoperative supplemental oxygen required to maintain SpO_2_ >90% Right to left intracardiac shunts Carotid stenosis defined as >50% stenosis of either carotid artery End-stage renal disease requiring haemodialysis Recent smoking (within 1 week) Planned regional anaesthesia	Intraoperative One lung ventilation Additional procedures other than CABG CPB more than once or circulatory arrest Fluid infusion rate more than 10 mL kg^–1^ h^–1^ post CPB Patients in restrictive oxygenation group needing FiO_2_ > 0.7 to maintain SpO_2_ ≥95% SpO_2_ < 90% lasting for more than 5 minutes
	Postoperative Non-respiratory reasons to reintubate Delayed extubation due to bleeding Delayed extubation due to heart failure	Any time Allogenic transfusion except less than 2 units RBC Circulatory assist device implantation (ECMO, VAD, or Impella^®^ device)

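### A withdrawal rule that only restrictive-arm patients can meet (needing FiO2 above 0.7) may remove poor oxygenators from one arm after randomisation, and its 0.7 conflicts with the abstract's 0.80 ceiling

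*Protocol article*

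**What the plan says.** **The rule.** Table 2 (Withdrawal Criteria, intraoperative) withdraws "Patients in restrictive oxygenation group needing FiO_2_ > 0.7 to maintain SpO_2_ ≥95"%. The Safety Assessment section, which describes the other withdrawals in prose, does not mention it.

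**The other arm.** Under Intervention and Anaesthetic Regimen: "The liberal oxygenation group receives 1.0 FiO_2_ throughout the intraoperative period, including during CPB".

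**Who applies it, and when.** Table 1 places allocation before oxygenation, so an intraoperative rule acts after randomisation. Study Design and Setting says that "the physicians who conduct the anaesthesia and monitoring intraoperatively in the operating room are unblinded".

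**What withdrawal means.** For the post-bypass fluid limit, which sits in the same intraoperative list: "otherwise, the patient will be withdrawn from analysis" (Intervention and Anaesthetic Regimen). For transfused patients: "these patients will also be withdrawn from our analysis" (Discussion). Sample Size Calculation adds: "Considering potential withdrawal, protocol violation, and failure to follow-up, we will aim to recruit 200 patients". The Discussion expects many withdrawals and describes them partly as a means of controlling bias.

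**The ceiling.** The abstract sets the restrictive arm's FiO2 at the lowest level needed, "but no less than 0.3 and not higher than 0.80 (other than induction and when the oxygenation goals cannot be reached"). The Methods text gives a minimum of 0.3 and no maximum.

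**The concern.** A comparison of randomised groups is protected only while departures from the analysis do not depend on arm. This rule names one arm, and the other arm has no way of meeting it. The only other intraoperative oxygenation rule, SpO2 below 90% for more than 5 minutes, is worded for both arms but is harder to trigger on pure oxygen, so it does not restore the balance.

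The patients it removes are those with poor gas exchange during surgery. They are the patients one would expect to have low PaO2/FiO2 afterwards. Taking them out of the restrictive arm alone raises that arm's mean, and the trial's hypothesis is that the restrictive arm does better. The staff who judge the need for more oxygen know the allocation.

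There is also a plain contradiction. A restrictive patient who needs FiO2 of 0.71 to 0.80 is within the permitted range in the abstract and is withdrawn under Table 2. Six centres (one in the USA, five in China) could apply different rules in that band.

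**Working it through.** **Inputs from the article.** Target difference 30 mmHg, SD 60 mmHg, two-sided alpha 0.05, 80 per arm after losses (Sample Size Calculation). Trigger FiO2 above 0.7 at SpO2 95% (Table 2). The Discussion adopts SpO2 95% "as our safe threshold because it is close to PaO_2_ 80mmHg".

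**The plan's own figures.** The article gives no figure for how often this rule will apply. Its loss allowance reproduces: 160/0.80 = 200. Its 160 does not: a two-sided t-test at 30/60 = 0.5 SD needs 64 per arm (128 in total) for 80% power, and 80 per arm gives about 88%. That difference is on the safe side and does not affect this point. The 80 per arm is used below only to set the standard error.

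**Inputs assumed.** The share p of the restrictive arm removed, the correlation r between intraoperative oxygenation and the primary outcome, normal distributions and no true treatment effect.

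**Formulas.** With z the normal quantile of p and φ the normal density:

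- Bias = r × 60 × φ(z)/(1 − p)
- SE = 60 × √(1/(80(1 − p)) + 1/80)
- Two-sided type I error = P(|Z + bias/SE| > 1.96)

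**Worked case, p = 5%, r = 0.5.** z = −1.645 and φ(z) = 0.1031. Bias = 0.5 × 60 × 0.1031/0.95 = 3.3 mmHg. SE = 60 × √(1/76 + 1/80) = 9.61. Bias/SE = 0.339. Type I error = 5.25% favouring restrictive + 1.08% favouring liberal = 6.3%.

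| Removed | r = 0.3 | r = 0.5 | r = 0.7 |
|---|---|---|---|
| 2% | 0.9 mmHg, 5.1% | 1.5 mmHg, 5.3% | 2.1 mmHg, 5.5% |
| 5% | 2.0 mmHg, 5.5% | 3.3 mmHg, 6.3% | 4.6 mmHg, 7.6% |
| 8% | 2.9 mmHg, 6.0% | 4.8 mmHg, 7.9% | 6.8 mmHg, 10.8% |

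A simulation of 200,000 trials with a t-test at r = 0.5 gave 5.2%, 6.2% and 8.0% for 2%, 5% and 8% removed. False positives favouring restrictive alone were 3.5%, 5.2% and 7.3%, against a nominal 2.5%.

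**What removal rate is plausible?** If SpO2 95% is close to PaO2 80 mmHg, needing FiO2 above 0.7 means an intraoperative ratio below about 80/0.7 = 114 mmHg. Borrowing the SD of 60, the share below that is Φ((114.3 − mean)/60):

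| Assumed mean ratio | Removed | Bias (r = 0.5) | Type I error |
|---|---|---|---|
| 300 | 0.1% | 0.1 mmHg | 5.0% |
| 250 | 1.2% | 0.9 mmHg | 5.1% |
| 225 | 3.3% | 2.3 mmHg | 5.6% |
| 200 | 7.7% | 4.7 mmHg | 7.7% |

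Removing 10% (5.8 mmHg and 9.2% at r = 0.5) would need a mean ratio below 200.

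**The case against.** **Removal from the analysis is not stated for this rule.** The explicit wording belongs to the fluid and transfusion rules. For return to bypass or circulatory arrest the Discussion speaks of withdrawal from the study, not from the analysis, and the abstract's exception for unmet oxygenation goals suggests such patients carry on. Analysis sets may be defined in a fuller document. This stands as a caveat. The inference is still well supported: the fluid rule is in the same list, the sample size allows for withdrawals, and withdrawal could control bias only if those patients leave the comparison.

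**The effect may be negligible.** At a mean ratio of 250 or more the model removes about 1% and type I error barely moves. The exclusions (severe COPD, preoperative oxygen, acute heart failure, recent smoking, high BMI) make low rates plausible. The SD is borrowed from a postoperative measure. A brief intraoperative need, before lung recruitment and the common ICU start at FiO2 0.5, may also predict the 48-hour minimum only weakly: at a mean of 225 and r = 0.3 the bias is 1.4 mmHg and type I error 5.2%. All of this stands, and it limits the weight of the point.

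**0.80 might cap the setting while 0.7 triggers withdrawal.** That is possible, but the article does not say so.

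**A rule for failed restrictive titration must be arm-specific.** That is true of stopping the assigned oxygen target, which is a clinical decision. It is no reason to drop the patient from the analysis.

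**Conclusion.** The point holds as a cheap improvement. The one-sidedness, the timing after randomisation, the unblinded trigger and the 0.7 versus 0.80 conflict are all on the page. The bias rests on two assumptions: that patients withdrawn under this rule leave the primary analysis, and that intraoperative oxygenation correlates with the postoperative minimum. Its direction, in favour of the restrictive arm, then follows.

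Its size cannot be fixed from the article. It runs from practically nothing if about 1% or fewer are removed to 2.9–6.8 mmHg (10% to 23% of the 30 mmHg target) at 8% removed, for correlations of 0.3 to 0.7. The lower end is plausible in this population. The case for changing the rule is that the bias has a known direction and can be avoided at almost no cost, not that it is large.

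**What to change.** 1. State one FiO2 ceiling for the restrictive arm, chosen by the clinicians, and use it in the abstract, the Methods and Table 2.
2. Delete the arm-specific criterion from the withdrawal list. Record need above the ceiling as rescue oxygen or a protocol deviation. Patients still receive whatever oxygen they need, so safety is unaffected.
3. State that the scheduled ICU blood gases continue in these patients (the article does not say whether they do after withdrawal) and that they stay in the primary analysis in the group to which they were randomised.

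The cost is wording edits, and the article says recruitment has not begun. The sample size does not rise. The one downside is a slight dilution of the contrast between arms from patients given rescue oxygen. With every randomised patient analysed, this selection bias is zero.

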### Safety Assessment

The PI, investigators, study coordinators, attending anaesthesiologists, and intensivists will be in close communication throughout the entire procedure until patient discharge to ensure protocol adherence. Patients will be withdrawn intraoperatively if they require 1 lung ventilation, additional procedures other than CABG, circulatory arrest, repeated episodes of CPB support, or usage of circulatory assist devices. If a patient suffers an SpO_2_ < 90% for more than 5 minutes at any time during the surgery, the patient will be withdrawn, and this will be recorded as a serious adverse event. Postoperatively, if a patient experiences delayed extubation (i.e., weaning/extubation period lasting longer than 48 hours) or requires reintubation for non-respiratory reasons (i.e., surgical reasons), suffers major bleeding (i.e., requiring a delay in extubation due to haemodynamic management), and develops heart failure, they will be withdrawn. If there is a perioperative allogenic RBC transfusion of more than 2 units or if a patient receives any other blood products, the patient will also be withdrawn (Table 2). Other postoperative events such as AKI, stroke, myocardial infarction, reoperation, and sternal wound infection will be recorded as adverse events and be analysed to determine whether they are related to the intervention. A trained research team member (i.e., fellow, study coordinator) will monitor the protocol compliance and report any adverse events to the IRB.

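### The transfusion withdrawal rule differs between three operative passages in red-cell threshold, products covered and time window, so who leaves the analysis depends on which passage a site follows

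*Protocol article*

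**What the plan says.** Three passages of the protocol article state an operative rule.

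- **Intervention and Anaesthetic Regimen:** withdrawal from the study follows "Transfusion of more than 2 units of red blood cells (RBCs), fresh-frozen plasma, platelets, or cryoprecipitate within 48 hours of ICU admission".
- **Safety Assessment:** the trigger is "perioperative allogenic RBC transfusion of more than 2 units or if a patient receives any other blood products". This sentence cites Table 2 as its reference.
- **Table 2, withdrawal criteria, under the Any time label:** "Allogenic transfusion except less than 2 units RBC".

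The Discussion returns to the subject when it explains the reason for withdrawal. It says that because "transfusion of blood products, in particular blood plasma, may cause lung injury, these patients will also be withdrawn from our analysis". It gives no threshold and no window. It also says: "We predict a high rate of withdrawal, not only for safety reasons but also for bias control and balancing of confounding factors".

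No passage says which statement prevails.

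**The concern.** Withdrawal here is a post-randomisation event with consequences for the analysis. The regimen section removes the patient from the study, and the Discussion speaks of removal from the analysis. If the trigger is ambiguous, so is the analysed population.

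Study Design and Setting describes six centres in two countries (one in the USA and five in China). The regimen section leaves the triggers for plasma, platelets and cryoprecipitate to laboratory values and clinical protocols, so exposure to those products may also vary by centre. Two sites could apply two different passages, each following the protocol. Patients with the same transfusion history would then be kept at one site and dropped at another.

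Timing raises a further question. The primary outcome is complete 48 hours after ICU admission. If Table 2's label is taken literally, a later transfusion withdraws a patient whose primary outcome already exists, and the document does not say whether that value is kept.

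**Working it through.** The plan gives no figure for this point, so the check sets the passages side by side and applies each one literally to test patients.

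**Elements of each rule**

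| Element | Intervention and Anaesthetic Regimen | Safety Assessment | Table 2 |
|---|---|---|---|
| Red cells | withdrawn above 2 units | withdrawn above 2 units | only fewer than 2 units spared |
| Other products | withdrawn above 2 units (plain reading) | any amount | any amount |
| Window | 48 hours from ICU admission | perioperative for red cells, none given for the rest | any time |

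**Applied to test patients.** Here, stays means only that the passage does not trigger withdrawal. The regimen window is taken to start at ICU admission.

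| Patient | Regimen | Safety Assessment | Table 2 |
|---|---|---|---|
| 1 red-cell unit in ICU | stays | stays | stays |
| Exactly 2 red-cell units in ICU, within 48 h | stays | stays | withdrawn |
| 3 red-cell units in ICU, within 48 h | withdrawn | withdrawn | withdrawn |
| 1 platelet unit in ICU, within 48 h | stays | withdrawn | withdrawn |
| 1 plasma unit in theatre only | stays | withdrawn | withdrawn |
| 3 red-cell units in theatre only | stays | withdrawn | withdrawn |
| 3 red-cell units, all after 48 h | stays | depends on what perioperative covers | withdrawn |

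**Pairwise comparison**

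- Regimen against Safety Assessment: they differ on the platelet unit, the theatre plasma unit and the 3 theatre red-cell units.
- Safety Assessment against Table 2: they differ at exactly 2 red-cell units, although the first cites the second.
- Regimen against Table 2: they differ on all of those and on the late transfusion.

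No two of the three passages classify every patient alike.

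**Sensitivity to the reading of the regimen section.** Its sentence can be parsed so that the 2-unit limit governs red cells only, with any amount of another product triggering withdrawal. The platelet row then becomes withdrawn in all three columns. The rows for 2 red-cell units, theatre plasma, theatre red cells and late red cells do not change. Disagreement falls from five of the seven test patients to four.

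These counts show where the texts diverge. They say nothing about how often such patients will occur.

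**The case against.** The strongest reply is that the rules are largely nested. If perioperative covers the first 48 hours in ICU, anyone withdrawn under the regimen section is also withdrawn under Safety Assessment, and anyone withdrawn there is also withdrawn under Table 2. Each passage gives a sufficient trigger, and the regimen section never says that other patients stay. A site that applies every criterion together arrives at Table 2. This is a fair account of how a careful site might proceed, but the document does not tell sites to do so. It also does not settle the case of exactly 2 red-cell units: a limit of more than 2 implies that 2 is tolerated, while Table 2 spares only fewer than 2.

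Two further replies stand in part. The product conflict depends on how the regimen sentence is parsed, as shown above. Any time is also a phase label in Table 2, beside preoperative, intraoperative and postoperative, so it may not have been meant to reach late transfusions. Neither reply removes the threshold conflict or the conflict over transfusions in theatre.

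Some stronger readings are tempting but unsupported:

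- **A fourth rule in the Discussion.** Taken literally, that sentence would withdraw a patient after one red-cell unit. It is written as rationale about transfusion-related lung injury and can be read as pointing back to the rule in the Methods. It is loose wording to be aligned.
- **A large share of the 200 patients affected, or power lost.** The document gives no transfusion rate. It calls transfusion common in cardiac surgery but adds that the rate in CABG is relatively low by comparison, and this trial enrols only isolated CABG. The predicted high withdrawal rate covers all causes and carries no number. Patients in dispute are not necessarily lost, since under the narrower texts they stay.
- **Unblinded investigators choosing the convenient passage.** Study Design and Setting says that the centre principal investigators are unblinded, but no passage gives them the withdrawal decision. Compliance monitoring is assigned to a trained fellow or coordinator.

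**Conclusion.** The point holds as a contradiction in a decision rule. The three operative passages disagree on the red-cell threshold and on the window and, on the plain reading of the regimen section, on the other products. The threshold conflict at exactly 2 red-cell units does not depend on how the regimen section's product list or window is read. The differences for one platelet or plasma unit, and for red cells given only in theatre, rest on a regimen window that starts at ICU admission or on the plain reading of its product list.

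The consequence is an analysis population that is not uniquely defined and could differ between sites. Its size cannot be stated from the document, and the verdict does not rest on any assumed rate. Nor does it rest on the Discussion sentence. This is a conflict within stated text, so it is not a detail that an article would simply leave to a fuller document.

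**What to change.** Before the first patient is enrolled:

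1. Reconcile Intervention and Anaesthetic Regimen, Safety Assessment and Table 2 into one rule with one red-cell threshold, one provision for other products and one window with a defined start and end. Place it in Table 2, have the other sections refer to it, and align the Discussion wording.
2. State whether a primary outcome that is already complete when a patient is withdrawn is retained.
3. Record units, product and time of each transfusion in the eCRF, so that withdrawal status is derived by program in the same way at every site.

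The choice of threshold, products and window belongs to the investigators.

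The cost is a wording amendment and one eCRF derivation, with no extra patients or procedures. Study Registration says that recruitment has not begun, so the change can be made now without reclassifying anyone. Once patients are enrolled, harmonising the rule would mean reclassifying them with data in hand.
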